#### **7.1.3.2 Protocol-specific exceptions for immediate SAE reporting**

As mentioned above (7.1.1), hematological toxicities as signs of an effective antileukemic treatment and an intended myelosuppression do not fulfil the definition of an AE and therefore cannot constitute an SAE.

Within this study, SAEs considered as either a sometimes inevitable complication of the intended antileukemic activity or as signs of progression of the underlying disease, are

exempted from immediate reporting. SAEs considered as complication of an intended antileukemic therapy include: neutropenic fever, neutropenic infections and thrombocytopenic bleedings. Signs of leukemia progression as judged by the investigator can be:

- neutropenic infections due to disease progression\*
- thrombocytopenic bleedings due to disease progression\*
- Deterioration of the general condition due to leukemia progression\*
- Laboratory abnormalities due to leukemia progression\*
- tumor lysis syndrome due to disease progression\*
- Organ failure due to leukemia progression\*: renal insufficiency, coagulopathy, respiratory failure, hypotension
- Death due to leukemia progression\*

\*leukemia progression defined as at least one of the following: reappearance of blasts in the peripheral blood, raising blast counts in the peripheral blood, raising blast counts in bone marrow, appearance, reappearance or progression of chloromas, raising lactate dehydrogenase serum level not otherwise explained

In those cases, page one of the SAE form has to be filled out and sent to the study office Muenster together with the corresponding CRFs within 4 weeks. The study office will forward it to the Safety Desk to be entered into the SAE database.

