##### **3.1.1 Benefit / risk ratio**

Patients eligible for this trial have a chance of survival with any other therapy of 25% after one year [2]. The risk of this trial is that addition of BIBF 1120 to low-dose cytarabine increases treatment-related death due to extensive toxicity. Since a MTD for BIBF 1120 monotherapy and for combination therapy with various cytotoxic agent has already been evaluated in clinical trials in solid tumors, it seems justified to perform an enhance dose finding for the combination therapy of BIBF 1120 and low-dose cytarabine.

The possible benefit of the trial is to decrease the rate of treatment failure in the trial population. For a single patient, this could result in increased life-span, ideally without evidence of leukemia. Given the extensively high rate of primary or secondary treatment failure in this patient population, the medical need for novel, rational therapeutic approaches for this patient population is overwhelming. As pointed out above, the molecular rationale for

the therapeutic administration of BIBF 1120 in AML is well founded. Thus, the benefit/risk ratio for a patient to participate in this trial appears favorable.

Since the application of 5-azacytidine has a proven efficacy in low-proliferating AML with  $\leq 30\%$  bone marrow blasts [17], AML patients with  $\leq 30\%$  bone marrow blasts should be treated with 5-azacytidine if possible. Accordingly, patients qualifying for an intensive treatment have a chance of achieving a complete remission of 50% and should therefore be treated with an intensive approach. However, no therapeutic approach exists in patients with  $>30\%$  bone marrow blasts and adverse cytogenetic risk unfit for an intensive treatment, and these patients have the highest need for therapy improvement. Patients with non-adverse cytogenetic risk and not qualifying for both therapy with 5-azacytidine and intensive chemotherapy only have an 18% chance of achieving a complete remission upon treatment with low-dose cytarabine alone. It therefore seems justifiable to include these patients (with AML not qualifying for both 5-azacytidine and intensive chemotherapy) into this trial.

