### 5.4.2 Phase I – part

The optimum dosage of BIBF 1120 in combination with low-dose cytarabine will be determined in a phase I part. Based on acceptable safety data for BIBF 1120 monotherapy, there will be a rapid dose finding. Dose finding will proceed in a classical 3+3-design. Predefined dose levels are: 100mg (dose level 1), 150mg, (dose level 2), and 200mg (dose level 3) twice daily. A cohort of three patients will be treated in each dose level and toxicity will be assessed in the first treatment cycle (28 days) by Common Terminology Criteria for Adverse Events V 4.0 (CTCAE). Patients evaluable for this safety analysis have to have received at least one dose of BIBF1120 and AraC. In case of no dose limiting toxicity (DLT), the dose will be increased by one dose level. In case of one DLT, up to three further patients will be recruited into the same dose level. If >1 DLT occurs in one dose level in up to six patients, this dose level will not be further evaluated. The highest dose level with  $\leq 1$  DLT out of six patients will be defined as the maximum tolerable dose (MTD) and will be evaluated in the phase II part of the study after approval of the data monitoring committee (DMC). Dose levels considered for phase II with less than six patients evaluated (i.e. no DLT in three patients) will further recruit patients until a total of six evaluable patients and will be chosen for phase II only if the aforementioned condition ( $\leq 1$  DLT out of six patients) applies. In case of >1 DLT in the dose level 1 cohort, the dose will be decreased to dose level 0 (100 mg BIBF 1120 once daily). The study will not proceed to the phase II part if >1 DLT occurs in dose level 0. A DLT is defined as every severe adverse reaction CTC grade IV with possible or definite relationship to the study drug BIBF1120. Therapy-related cytopenias as signs of an intended antileukemic activity do not fulfill the definition of an adverse events and therefore cannot constitute an SAE or DLT. The following known, frequent and often inevitable complications from therapy-related cytopenias are also excluded from DLT: neutropenic fever, neutropenic infections and thrombocytopenic bleedings. Notwithstanding, these complications may constitute a DLT if occurring in an unexpected high frequency, as judged by the DMC, and should be reported as an AE or SAE as appropriate (see 7). Complications attributable to disease progression in the judgement of the investigator are also excluded from DLT. These include:

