### **7.1.3 Serious Adverse Event (SAE) or Serious Adverse Reaction (SAR)**

A serious adverse event or serious adverse reaction is any untoward medical occurrence or effect that at any dose

- results in death,
- is life-threatening,
- requires hospitalization or prolongation of existing inpatients' hospitalization,
- results in persistent or significant disability or incapacity,
- is a congenital abnormality or birth defect.

Comments:

- All deaths up to and including 28 days after the last protocol treatment and death after the observational period (28 days after the last protocol treatment) which deemed to be related have to be reported immediately on an SAE form with one exemption (for exemptions from immediate reporting see 7.1.3.2). The adverse event is the underlying event which caused the death.
- Life-threatening in the definition of a serious adverse event or serious adverse reaction refers to an event in which the subject was at risk of death at the time of event; it does not refer to an event which hypothetically might have caused death if it were more severe.
- Hospitalization means overnight admission.
- Hospitalization without underlying adverse event (AE) is not an SAE. Examples are:
  - Hospitalization for protocol procedures e.g. chemotherapy
  - Elective hospitalization for a pre-existing condition (i.e. a condition other than the indication for the chemotherapy) that has not worsened
  - Hospitalisation which was already planned at the beginning of the trial. Hospitalisation must have been reported at screening visit in the source data and have been performed as planned
  - Admission to a rehabilitation centre or hospice

- Hospitalization for administrative or social reasons (e.g. due to anxiety but otherwise treatable on an outpatient basis).
- Congenital abnormality or birth defect: Fathering a child under BIBF 1120 is reportable as SAE in order to identify and follow-up on outcome of pregnancy and on any congenital abnormalities. The report should be made as soon as the investigator gets knowledge of the pregnancy. Follow-up of each pregnancy will be done using specific additional questionnaires supplied by the Safety Desk. Study participants will be informed about the necessity to follow up any pregnancy starting under study participation and are requested to consent into a follow-up of the course of any pregnancy in the patient information and informed consent.

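### Sections 7.1.3 and 7.1.3.2 conflict on whether a fatal neutropenic infection or thrombocytopenic bleeding attributed to treatment must be reported immediately

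*Protocol*

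**What the plan says.** Three sections of the protocol govern this.

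- **Section 7.1.3** sets the rule for deaths. "All deaths up to and including 28 days after the last protocol treatment", and later deaths thought to be related, "have to be reported immediately on an SAE form with one exemption (for exemptions from immediate reporting see 7.1.3.2". It adds how a death is to be recorded: "The adverse event is the underlying event which caused the death".
- **Section 7.1.3.2** takes two classes of SAE out of immediate reporting. The first is complications of the treatment's intended effect: "SAEs considered as complication of an intended antileukemic therapy include: neutropenic fever, neutropenic infections and thrombocytopenic bleedings". The second is signs of leukemia progression, a list that includes death from progression. For both classes, page one of the SAE form is to be "sent to the study office Muenster together with the corresponding CRFs within 4 weeks". The study office then passes it to the Safety Desk; no time limit is given for that step.
- **Section 7.2** requires the remaining SAEs to reach the Safety Desk by fax within 24 hours of the investigator learning of them, whatever their relationship to study drug. It sets the 7.1.3.2 exceptions aside before applying that limit.

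Two other sections matter for the consequences. Section 3.1.1 names as the risk of the trial that adding BIBF 1120 "increases treatment-related death due to extensive toxicity". Section 5.4.2 excludes the same three complications from the DLT definition, but "these complications may constitute a DLT if occurring in an unexpected high frequency, as judged by the DMC".

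**The concern.** Infection and bleeding during cytopenia are a natural form for a treatment-related death to take in this trial, and they are the events in the first exempt class. If a site treats such a death as exempt, the Safety Desk may learn of it weeks later than it would of any other fatal SAE.

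Three activities depend on receipt of the form:

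- the coordinating investigator's second review of seriousness, relatedness and expectedness (section 7.2, which makes outcome part of expectedness and counts a clinically important rise in the rate of a known reaction as unexpected);
- the Safety Desk's duty to pass on suspected unexpected serious reactions;
- in phase I, the DMC's judgement of whether these complications are too frequent, which is the only way they can count as DLTs.

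**Working it through.** The protocol has no figure to reproduce here. The check is a comparison of texts, with one subtraction.

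**Step 1: follow one case through the rules.** Take a patient who dies of neutropenic sepsis during cycle 1. The investigator attributes it to treatment and not to progression.

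| Rule | Result |
|---|---|
| 7.1.3, deaths | A death within the window, so immediate, unless it is the one exemption |
| 7.1.3.2, deaths named | Only death from leukemia progression; this is not one, so immediate |
| 7.1.3, how a death is recorded | Recorded as the causal event: a neutropenic infection |
| 7.1.3.2, first class | Neutropenic infection as a complication of therapy, with no limit on outcome, so exempt |
| 7.2, 24-hour rule | Applies only to what 7.1.3.2 has not removed, so it does not settle the matter |

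The same death is immediately reportable on rows 1 and 2 and exempt on rows 3 and 4. A fatal thrombocytopenic bleeding gives the same result.

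**Step 2: is the first class really treatment-attributed?** Section 7.1.3.2 lists neutropenic infections and thrombocytopenic bleedings a second time, under progression. The first class is therefore the group ascribed to therapy. It is not a duplicate of the progression group.

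**Step 3: the difference in time.** Inputs: 24 hours (7.2); 4 weeks (7.1.3.2); 2 weeks for phase I CRFs (9.5), which may govern because the exempt form travels with the CRFs.

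- 4-week route: 4 × 7 − 1 = 27 days later, plus forwarding.
- 2-week route, phase I: 2 × 7 − 1 = 13 days later, plus forwarding.

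These are upper limits for the step to the study office and assume both clocks start together. Section 7.1.3.2 does not say when the 4 weeks begin. The forwarding step has no upper limit.

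**Step 4: phase I.** DLTs are assessed over a 28-day first cycle (5.4.2), and the DMC receives a safety report after each dose level (9.1). For an event on day *d* of that cycle, the form may be due at the study office as late as day *d* + 28, which is after day 28 for every *d*. On the 2-week reading it is day *d* + 14, which is after day 28 when *d* > 14. Nothing requires exempt forms to be in hand before the DMC report is prepared. How long passes between the end of the window and that report is not stated, so the text leaves a late form possible but does not show that one would miss the report.

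**The case against.** The strongest reply is that the sections can be read in harmony. Section 7.1.3 speaks of one exemption and cross-refers to 7.1.3.2, and 7.1.3.2 contains exactly one death item. On that reading a fatal treatment-attributed infection is plainly reportable within 24 hours. This is a fair reading and may well be what was meant. But the underlying-event sentence and the open wording of the first class support the other reading equally well, and nothing tells a site which prevails.

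Other points stand in part:

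- The exemption is not unlimited. It covers events regarded as complications of the intended antileukemic effect, so infection without neutropenia and bleeding without thrombocytopenia stay under the 24-hour rule.
- Phase I has safeguards: 2-week CRFs (9.5), a DMC report after each dose level (9.1) and monitoring of all patients (9.3). They reduce the exposure. None sets a time for exempt forms to reach the Safety Desk.
- Exempting common cytopenic complications from rapid reporting is a deliberate choice and consistent with the DLT definition.

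Some stronger inferences are not supported. A reader might conclude that 7.1.3.2 expressly exempts fatal events suspected to be related to BIBF 1120; it does not, and that result follows only from its silence. A reader might size the problem from the 13% treatment-related bleeding in section 7.3.1.1; that figure includes anemia and epistaxis, is not limited to serious events, and comes from combinations with other drugs. A reader might turn 122 patients in 24 months into a number treated during the delay; this assumes that phase II alone fills the accrual period, that the full 4 weeks is used, and that earlier review would have halted entry. The protocol states none of these. Finally, since expectedness rests on the Investigator's Brochure, which is not shown, a late report of an unexpected reaction is possible but cannot be demonstrated.

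**Conclusion.** The point holds as an unresolved conflict over fatal events. It is partly an ambiguity, because 7.1.3 defers to 7.1.3.2, but the literal wording of 7.1.3.2 sends a fatal treatment-attributed neutropenic infection or thrombocytopenic bleeding by the slow route. The size is a delay of up to 27 days to the study office compared with the 24-hour rule (13 days if the 2-week CRF limit governs phase I), plus forwarding of unstated length. The number of patients affected cannot be estimated from the protocol.

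The conclusion assumes that a site follows the first-class wording together with the underlying-event sentence, and uses the time allowed. It does not depend on any view of whether exempting non-fatal complications is wise, and it gives no ground for narrowing the exemption by suspected relationship to BIBF 1120. The first class consists of therapy complications by definition, so such a limit could largely empty it; that is a trade-off for the sponsor. What remains is narrow, but it concerns the reporting of deaths and can be settled with a few sentences.

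**What to change.** Amend sections 7.1.3, 7.1.3.2 and 7.2 so that they agree:

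1. State in 7.1.3.2 that the exemption for complications of therapy covers non-fatal events only.
2. State in both 7.1.3 and 7.1.3.2 that death from leukemia progression is the only death exempt from immediate reporting. A fatal infection or bleeding attributed to progression then falls under that item; one attributed to therapy does not.
3. Give the study office a deadline for forwarding exempt forms to the Safety Desk, and say when the site's own clock starts.
4. In phase I, align the deadline for exempt forms with the 2-week CRF limit in 9.5, and require these forms to be included in the DMC safety report for each dose level.

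The cost is amendment wording and some additional 24-hour reports. These should be few, since only fatal events are added, although the protocol gives no rate from which to count them. The exemption for non-fatal cytopenic complications stays as designed.

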## 7.2 Period of observation, documentation and reporting

All AEs, including SAEs, will be recorded from the time of signing the informed consent until 28 days after last protocol treatment including low-dose cytarabine. Medical judgment should be used to determine the relationship, considering all relevant factors, including pattern of reaction, temporal relationship, de-challenge or re-challenge, confounding factors such as concomitant medication, concomitant diseases and relevant history. Assessment of causal relationship must be recorded for each adverse event

All AEs, including SAEs, have to be recorded on the appropriate adverse event pages in the CRF.

Documentation and assessment by the investigator includes:

- Diagnosis or Description of AE
- Date of onset and date of end of AE
- Seriousness (yes/no)

- Severity, graded according to the National Cancer Institute Common Terminology Criteria for Adverse Events (CTCAE) v 4.0 for Cancer Clinical Trials
- Causality (reasonable possibility/no reasonable possibility)
- Action taken with investigational medicinal drug (none/dose changed/drug temporarily withdrawn/drug permanently withdrawn)
- Outcome (recovered/resolved, recovering/resolving, not recovered/not resolved, recovered/resolved with sequelae, fatal, unknown)

If possible, a diagnosis rather than a list of signs, symptoms and laboratory abnormalities should be given.

All AEs, including SAE, must be followed up until the condition resolves or stabilizes. (For definition of resolution of an adverse event please see 5.4.4.1.)

All SAEs identified by the protocol as requiring immediate reporting (for exceptions, see 7.1.3.2) and all AEs of special interest (for definition, see 7.1.3.1) must be reported on the SAE form in English and transmitted by fax to the Safety Desk within 24 hours of knowledge by the investigator. This applies regardless of severity (CTCAE v 4.0 grade) and whether or not the SAE is considered related to the use of study drug by the investigator. Personal data have to be replaced by the patient registration number before forwarding any information. SAEs requiring immediate reporting will be reported to Boehringer Ingelheim by the sponsor within the format and the timelines specified in the contract between sponsor and Boehringer Ingelheim.

Where possible, a diagnosis rather than a list of symptoms should be given. The investigator is responsible for assessment of seriousness, severity (CTCAE v 4.0) and causality of the SAE. The SAE form should be completed with as much information as possible. All relevant information should be documented on the SAE form. Additional documents like medical reports should only be attached if necessary, and if so, relevant information should be clearly marked. The investigator should not wait for full details before making the initial report.

|                                                                                                                                                                 |
|-----------------------------------------------------------------------------------------------------------------------------------------------------------------|
| Safety-Desk-Contact                                                                                                                                      |
| Zentrum für Klinische Studien (ZKS) Münster
[name]
[name]
[contact]
[contact]
E-Mail: [contact] |

If the event is fatal or life threatening, the investigator must fax any relevant follow-up information of the reported SAE to the Safety Desk within 8 days from the initial report. In case of death, a pseudonymized copy of the autopsy protocol should be provided to the Safety Desk, if any. For SAEs which are not fatal or life threatening, the investigator must fax follow-up information as soon as possible. Information about all non-serious AEs occurring at the same time and/or which are medically related to the SAE have to be added (copies of the AE forms).

The investigator should answer any queries from the Safety Desk and Boehringer Ingelheim as soon as possible. In case of death, the investigator also has to supply the competent authority and the Ethics Committee with any details, if requested by them.

If the investigator suspects a reasonable causal relationship to the investigational medicinal product and/ or study design in an SAE occurring after the end of the reporting period, this event may also be reported to the Safety Desk. The investigator is explicitly encouraged to report late serious adverse reactions which are not yet listed in the Investigator's Brochure. Late SAEs do not have to be recorded on the adverse event page of the CRF. Reporting to the Safety Desk may be done on an SAE form or formless.

#### Assessment of serious adverse events by the sponsor

The Safety Desk will document each SAE, check it and query additionally required information. The Coordinating Investigator will review each SAE again for seriousness and relatedness.

Furthermore the Coordinating Investigator will assess whether an SAR is expected or unexpected according to the Investigator's Brochure and whether any SAE might influence the benefit-risk-ratio or require changes in the conduct of the trial.

“Unexpected” means that the nature, severity or outcome of the adverse reaction is not consistent with the applicable product information (Investigator's Brochure).

- The term “severe” is often used to describe the intensity (severity) of a specific event. This is not the same as “serious,” which is based on patient/event outcome or action criteria.

Examples of unexpected events include:

- A more specific reaction than labelled (“acute renal failure” is a labelled AR, a new report of “interstitial nephritis” is more specific and therefore unexpected).
- An increase in the rate of occurrence of an expected AR, which is judged to be clinically important, is considered as unexpected.

A suspected unexpected serious adverse reaction (SUSAR) is a serious adverse reaction that has been judged to be unexpected.

